# General Anesthesia versus Local Anesthesia in StereotaXY (GALAXY) for Parkinson’s disease: study protocol for a randomized controlled trial

**DOI:** 10.1186/s13063-017-2136-8

**Published:** 2017-09-07

**Keywords:** Neurosurgery, Parkinson’s disease, Deep brain stimulation, Prospective randomized open-label blinded endpoint trial

## Abstract

**Background:**

The aim of the study is to investigate if deep brain stimulation (DBS) in the subthalamic nucleus (STN) for Parkinson’s disease (PD) under general anesthesia further improves outcome by lessening postoperative cognitive, mood, and behavioral adverse effects; shorten surgical time and hospital admittance; and produce comparable symptomatic and functional improvement to surgery under local anesthesia.

**Methods/design:**

The study will be a single-center, prospective, randomized, open-label, blinded endpoint trial comparing DBS under general anesthesia with DBS under local anesthesia. The primary outcome measure is a composite score of the postoperative cognitive, mood, and behavioral adverse effects and will be measured 6 months after surgery. The secondary outcome measures consist of changes in motor symptoms, adverse effects of stimulation and surgical complications, surgical time, functional health, quality of life, patient satisfaction with the outcome of treatment, patient evaluation of the burden of therapy, and medication. A total of 110 patients with advanced PD who are candidates for DBS will be randomized during a 2.5-year period.

**Discussion:**

The aim of this trial is to further enhance the effectiveness of DBS treatment in PD while reducing the burden of DBS surgery by studying if DBS surgery under general anesthesia results in less cognitive, mood, and behavioral adverse effects compared with surgery under local anesthesia.

**Trial registration:**

Netherlands Trial Register, NTR5809. Registered on 23 April 2016.

**Electronic supplementary material:**

The online version of this article (doi:10.1186/s13063-017-2136-8) contains supplementary material, which is available to authorized users.

## Background

Continuous deep brain stimulation (DBS) of the subthalamic nucleus (STN) is an effective surgical treatment for patients with advanced Parkinson’s disease (PD) who have severe limitations in functioning despite optimal pharmacological treatment [1–5]. Currently, the standard DBS procedure is performed under local anesthesia, which is very burdensome for patients. Due to advances in modern imaging techniques, it is now possible to visualize the DBS target directly [6–9]. Surgery for DBS could therefore be performed under general anesthesia. The literature shows an overall comparable outcome measured with the Unified Parkinson’s Disease Rating Scale (UPDRS [10]) and Movement Disorder Society-sponsored revision of the UPDRS (MDS-UPDRS [11]) motor score in STN DBS under general anesthesia and STN DBS under local anesthesia [12–22]. There is little evidence about the rate of adverse events in STN DBS under general anesthesia [17, 18, 21]. Furthermore, the effect of general anesthesia on cognitive, mood, and behavioral adverse effects is poorly investigated [21, 23]. STN DBS under local anesthesia is very burdensome for all patients and holds back some who are actually good candidates for the procedure. We hypothesize that STN DBS under general anesthesia would be much less traumatic for patients and would lead to less cognitive, mood, and behavioral adverse effects. To our knowledge, no randomized controlled trial has been done to compare the outcome of STN DBS in patients who undergo the surgery under general anesthesia versus local anesthesia. We aim to investigate whether STN DBS under general anesthesia will further improve outcome by lessening postoperative cognitive, mood, and behavioral adverse effects 6 months after surgery; shorten surgical time and hospital admittance; and produce comparable symptomatic and functional improvement to that of surgery under local anesthesia.

## Methods/design

### Trial design

In this study, using a prospective, randomized, open-label, blinded endpoint (PROBE) study design, we will assess the effectiveness of STN DBS surgery under general anesthesia compared with the current standard practice of surgery under local anesthesia. The study schedule is shown in Additional file 1: Figure S1.

### Setting

The protocol of this single-center study was approved by the Medical Ethics Committee of the Academic Medical Center (AMC), Amsterdam, The Netherlands. It is registered with the Netherlands Trial Register (NTR5809). Inclusion and randomization of the study started on May 23, 2016.

### Participants

The inclusion criteria are (a) idiopathic PD with bradykinesia and at least two of the following signs: resting tremor, rigidity, and/or asymmetry; (b) despite optimal pharmacological treatment, at least one of the following symptoms: severe response fluctuations, dyskinesias, painful dystonia, or bradykinesia; (c) older than 18 years of age; and (d) a life expectancy of at least 2 years. Exclusion criteria are (a) legally incompetent adults; (b) previous PD-related neurosurgery (e.g., DBS, pallidotomy, thalamotomy); (c) contraindications for DBS surgery, such as a physical disorder making surgery hazardous; (d) Hoehn and Yahr stage 5 at the best moment during the day; (e) current psychosis; (f) current depression; and (g) no written informed consent.

### Study procedures

Patients are referred to the AMC by their treating neurologist for the indication of DBS. According to regular DBS care, the patients are admitted for several days to evaluate the following: disease severity; response to PD medication; and cognition, mood, and behavior. After this screening, the patient is discussed in a multidisciplinary meeting with the neurologist, neurosurgeon, neuropsychologist, psychiatrist, and specialized nurse in order to decide if the patient is eligible for surgery.

When the patient is a good candidate for DBS surgery, the attending neurologist/neurosurgeon will check inclusion and exclusion criteria for the study. If the patient is eligible, the physician coordinating the study will inform the patient, hand over written information about the trial, explain the trial to the patient, and subsequently ask the patient to consider participation. The consent procedure is further described below under the “Ethics approval and consent to participate” heading. After signing the informed consent form, the patient will be randomized.

### Randomization

The randomization procedure will be website-based using random blocks and stratified by the response to a suprathreshold levodopa dose administered in off-drug phase. This response is measured as the ratio of the MDS-UPDRS part III score in on-/off-drug phases. The response to levodopa is a good indicator of the effect of DBS. A cutoff of 40% improvement in MDS-UPDRS in on-drug phase was used to separate the two stratification groups. The cutoff is based on the median improvement of patients treated with DBS in the STN in a previous nationwide study on the effectiveness of DBS in patients with PD [24]. The web-based method of randomization will provide concealment allocation and prevent the risk of selection bias. Participants will be randomized using TENALEA, which is an online, centralized randomization service. Allocation concealment will be ensured because the service will not release the randomization code until the patient has been recruited into the trial, which takes place after all baseline measurements have been completed, as shown in Additional file 1: Figure S1.

### Intervention

DBS treatment is performed by a team that consists of various specialties (e.g., neurologist, neurosurgeon, specialized nurses). Treatment is in accordance with the usual care regarding this procedure. A neurosurgeon places two electrodes in the brain. These are connected to an implantable pulse generator. All patients will receive anesthetics during placement of the pulse generator. Currently, patients are hospitalized for 4 days, on average. On the day of surgery, patients do not receive PD drugs until the end of the procedure.

#### Local anesthesia

The stereotactic technique will be employed for implantation with the Leksell stereotactic frame (Elekta, Stockholm, Sweden) and guided by magnetic resonance imaging (MRI). For this part of the surgery, patients will have the stereotactic frame attached to the head under local anesthesia, after which an MRI scan is obtained and the implantation of electrodes is carried out. The decision for electrode placement is based on MRI scan, microelectrode recordings (three channels), and intraoperative macroelectrode stimulation effects. Two electrodes will be implanted, one in each STN. Subsequently, patients will have a second surgery under general anesthesia to implant the pulse generator subcutaneously in the subclavian area. The electrodes are connected to the pulse generator.

#### General anesthesia

The stereotactic technique will be employed for implantation with the Leksell stereotactic frame (Elekta, Stockholm, Sweden) and guided by MRI. Patients receive general anesthesia before the stereotactic frame is fitted to the head. The decision for electrode placement is based on MRI and microelectrode recordings (two to three channels). In contrast to the local anesthesia group, no macroelectrode stimulation will be performed. The electrodes will be implanted into the STN. In the same procedure, patients will undergo implantation of the pulse generator subcutaneously in the subclavian area. The electrodes are connected to the pulse generator.

During follow-up, the use of oral comedication is allowed in both groups just as in regular daily practice and current DBS treatment. The treating neurologist supervises any changes in medication. The main motivation for this approach is to stay close to regular daily practice routines for reasons of generalizability.

### Outcome measures

#### Primary outcome measure

The primary outcome measure is the number of patients with significant postoperative cognitive, mood, and behavioral adverse effects as indicated by a stringent composite score of ≥ 1 within 6 months after STN DBS. Significant cognitive, mood, and behavioral adverse effects are defined in four areas: (a) deterioration of cognition in three domains or more would lead to assigning a point for cognition on the composite endpoint; a Reliable Change Index less than or equal to −1.645 on at least one subtest per domain would lead to the conclusion of deterioration in this domain [25]; (b) loss of professional activity, work, or job; (c) postoperative delirium assessed with the Confusion Assessment Method [26] and the Delirium Observation Scale [27]; or (d) psychosis, depression, or anxiety for a period of 3 months or longer as defined by the Mini International Neuropsychiatric Interview psychiatric assessment [28] (Additional file 2: Table S1).

#### Secondary outcome measures

Secondary endpoints are the efficacy of treatment on the following:Motor symptoms as measured by MDS-UPDRS part III and the Clinical Dyskinesia Rating Scale [29]Daily functioning measured with MDS-UPDRS part IINonmotor experiences of daily living as measured by MDS-UPDRS part IFunctional health status measured with the Academic Medical Center Linear Disability Score [30]Quality of life measured with the 39-item Parkinson’s Disease Questionnaire (PDQ-39) [31]Treatment satisfactionBurden of therapySurgical timeDuration of hospital admittanceSurgery- and stimulation-related side effectsPD medication changesOther motor complications measured with UPDRS part IVOther psychiatric adverse effects as measured with the Hamilton Depression Rating Scale [32], Hamilton Anxiety Rating Scale [33], Columbia Suicide Severity Rating Scale [34], Starkstein Apathy Scale [35], and Young Mania Rating Scale [36]

*See* Additional file 3: Table S2 for further details.

### Sample size calculation

We estimate that by performing DBS surgery under general anesthesia, a relative reduction of 50% in cognitive, mood, and behavioral adverse effects will be achieved. To detect a relative reduction of 50% (52% local anesthesia versus 26% general anesthesia) using a chi-square test with an α value of 0.05 (two-sided) and β value of 0.2, we estimated that 110 patients (55 in each treatment group) would be needed. We expect adequate participant enrollment to reach our target sample size because we operate on 80 patients with PD per year. Furthermore, in our previous clinical trials, we have always been able to reach an inclusion ratio of 70% when studying patients with PD.

### Statistical analysis

Statistical analyses will be based on the intention-to-treat principle. Baseline assessments and outcome parameters will be summarized using simple descriptive statistics. Change scores are calculated as the score at follow-up minus the score at baseline. To test the hypothesis that STN DBS under general anesthesia produces fewer patients with significant postoperative cognitive, mood, and behavioral adverse effects, the primary outcome score will be compared using a chi-square test. Adjustments for factors that differ at randomization, including the stratification variable, will be made using regression or multilevel models. Effect sizes will be expressed as ORs. We will perform additional per-protocol and as-treated analyses.

The mean change in MDS-UPDRS Part III scores from baseline to follow-up at 6 months will be analyzed using a two-group *t* test. With regard to the comparisons of the other secondary outcomes, we will use the appropriate parametric and nonparametric statistics. Additionally, we will focus on the MDS-UPDRS part III scores at 6 months using multivariable linear regression, including the stratification variable and other factors that differ at randomization, in the model. In all analyses, statistical uncertainty will be expressed with 95% CIs. *P* values < 0.05 will be considered statistically significant. We will perform additional per-protocol and as-treated analyses. A fully specified statistical analysis plan will be written and approved before unlocking the data blinding, provided in the form of a *Trials* Update article.

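### Covariates for the adjusted analyses are chosen by chance imbalance, not prognostic value, and the rank of the adjusted model beside the chi-square test is not stated

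*Protocol article*

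**What the plan says.** In the protocol article, Statistical analysis, the hypothesis on the composite endpoint is tested thus: "the primary outcome score will be compared using a chi-square test". The next sentence reads: "Adjustments for factors that differ at randomization, including the stratification variable, will be made using regression or multilevel models". Then: "Effect sizes will be expressed as ORs", without saying whether the adjusted or the unadjusted odds ratio is meant. The MDS-UPDRS part III score gets a t test and additionally a linear regression, "including the stratification variable and other factors that differ at randomization, in the model". No criterion for a difference is given, and no list of candidate factors.

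The Randomization section describes a concealed web-based allocation in random blocks, "stratified by the response to a suprathreshold levodopa dose administered in off-drug phase", with two strata. The Sample size calculation rests on the unadjusted test: "using a chi-square test with an α value of 0.05 (two-sided) and β value of 0.2", with rates of "52% local anesthesia versus 26% general anesthesia". A full SAP is promised before unblinding; it is not at hand.

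**The concern.** With concealed randomization, any baseline difference between arms arises by chance. A rule that adjusts for whatever happens to differ has two defects. The covariate set is known only after baseline data have been compared by arm, so the model depends on the realised allocation. And the rule selects on the wrong property: a covariate improves precision because it predicts the outcome, not because it is unbalanced. A strong predictor that happens to be balanced is left out, and an irrelevant factor that happens to differ goes in.

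The levodopa-response stratum shows the confusion. Stratified blocks hold it in near balance, so it is the factor least likely to differ. The sound reason to adjust for it is that the randomization used it.

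Two lesser matters follow. The chi-square has no stratum term, so if the stratum is prognostic the test is somewhat conservative. And the adjusted model has no stated rank, so it is unclear which odds ratio is the main estimate.

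**Working it through.** **1. The plan's own figure.** Inputs from Sample size calculation: p1 = 0.52, p2 = 0.26, mean 0.39, two-sided α 0.05 (z = 1.960), power 0.80 (z = 0.8416).

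n per arm = [1.960·√(2·0.39·0.61) + 0.8416·√(0.52·0.48 + 0.26·0.74)]² / 0.26² = (1.352 + 0.560)² / 0.0676 ≈ 54.1, rounded up to 55, so 110 in all. This agrees with "we estimated that 110 patients (55 in each treatment group) would be needed".

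Power at 55 per arm = Φ[(0.26·√55 − 1.352)/0.665] = Φ(0.867) = 80.7%. The exact binomial power of the chi-square without continuity correction is 81.1%. Both figures assume that all 110 patients have an outcome.

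**2. How often something differs.** Assume k independent baseline factors, each judged at P<0.05. P(at least one differs) = 1 − 0.95^k: 40% for k = 10, 64% for k = 20. The protocol gives neither k nor the threshold.

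**3. What omitting the stratum costs.** Simulation with 100,000 trials, 110 patients, two near-equal strata balanced by arm, chi-square against the stratified Cochran-Mantel-Haenszel (CMH) test. The stratum odds ratio is assumed. Differences are from unrounded values.

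| Stratum OR | Chi-square power | CMH power | Difference (points) |
|---|---|---|---|
| 1 | 81.0% | 80.5% | −0.5 |
| 2 | 81.3% | 81.8% | +0.5 |
| 3 | 81.8% | 83.5% | +1.8 |
| 4 | 82.3% | 84.8% | +2.5 |
| 9 | 83.8% | 89.1% | +5.3 |

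At a common event rate of 39%, the chi-square's type I error is 4.8% at stratum OR 2 and 3.9% at OR 4; the CMH test stays near 5%.

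**4. What the selection rule recovers.** Simulation with 8,000 trials, 112 patients, stratum OR 2, ten independent baseline covariates of which two are prognostic. Selection means a baseline difference at P<0.05. All three logistic models include the stratum.

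| OR per SD of the two covariates | Chi-square | Stratum only | Stratum + selected by imbalance | Stratum + two prespecified |
|---|---|---|---|---|
| 1.0 | 81.0% | 82.0% | 81.4% | 82.2% |
| 1.5 | 81.8% | 82.6% | 82.3% | 85.0% |
| 2.0 | 81.7% | 82.2% | 82.1% | 88.0% |

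The imbalance-selected model gains 0.3 to 0.5 points over the chi-square and does no better than the stratum alone, so that small gain comes from the stratum and not from the selected factors. At OR 1.5 to 2.0, prespecification gains 3.2 to 6.3 points over the chi-square, or 2.4 to 5.8 over the stratum-only model. A second simulation with OR 1.6 to 2.2 per SD gave 80–81% for selection, 81–82% for the chi-square and 83–88% for prespecified covariates.

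**5. What a free choice between the two P values would do.** Taking whichever of the chi-square and the imbalance-selected model is significant gives a type I error of 5.1 to 5.5% in the simulation of step 4 and about 6% in the second one. In step 4 the two analyses disagree on significance in 1 to 2% of null trials and 2.5 to 3.8% of trials under the planned effect.

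**6. Why the choice of odds ratio matters.** The marginal OR for the planned rates is (0.26/0.74)/(0.52/0.48) = 0.324. Take two equal strata with stratum OR 4 and the same marginal rates. The stratum risks are then 68.6% and 35.4% under local anesthesia (mean 52.0%), and 38.5% and 13.5% under general anesthesia (mean 26.0%). The OR within each stratum is about 0.29. Adjusted and unadjusted ORs therefore differ even with perfect balance.

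**The case against.** The protocol ties the hypothesis to the chi-square and sizes the trial on it, so the adjusted model reads most naturally as supportive. A full SAP is due before unblinding, and ranking analyses is ordinary SAP content. The quoted sentence does bring the stratum into the adjusted model. No figure in the document shows that the stratum, age or cognition predicts the composite; levodopa response is linked only to the effect of DBS. The baseline comparison is described as descriptive, so the P<0.05 screen is an assumption.

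Most of this stands, and it rules out three stronger readings that a reader might infer:

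- That there are two primary analyses to pick from after unblinding. Nothing names the adjusted model as primary; it simply has no label, and step 5 shows that even a free choice would do little harm.
- That the plan loses its 80% power. It does not, because the calculation already assumes the unadjusted test.
- That the stratification factor is ignored. It is missing from the chi-square only.

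What the objection does not rescue is the selection rule itself. It is stated text, given twice, and an SAP that followed it faithfully would still have a covariate set driven by the data.

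**Conclusion.** The rule for choosing covariates is unsound and should be replaced for both the primary outcome and MDS-UPDRS part III. This is a prespecification defect of moderate weight, not an error in the sample size or in the choice of primary test.

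The cost is a forgone gain: about 2 to 6 points of power in the adjusted model if two covariates have an OR of about 1.5 to 2.2 per SD, and about 0 to 2.5 points from the stratum alone at a stratum OR of 1 to 4. All these odds ratios are assumed. If neither stratum nor covariates predict the composite, there is essentially nothing to gain. The missing rank of the adjusted model and the undefined main odds ratio are real but smaller points. A reader might also conclude that the chi-square must give way as the primary test; the documents and the numbers do not require that.

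**What to change.** Before unblinding, in the SAP:

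- Delete the selection by difference at randomization in both places.
- Specify the adjusted model as treatment, the levodopa-response stratum and a short list of prognostic baseline covariates, for example age and baseline cognition, kept whatever the observed balance. For MDS-UPDRS part III, fix a list in the same way.
- State which single analysis and which odds ratio are primary, and label the other supportive. Keeping the chi-square as primary, or replacing it with a stratified CMH test, is acceptable.
- Report a risk difference or a standardized estimate beside the adjusted odds ratio.

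The cost is wording only. The Randomization section places recruitment after all baseline measurements, and Study procedures lists cognition, mood and behavior among the screening assessments. Expected events are 55·0.52 + 55·0.26 = 42.9; with four coefficients (treatment, stratum, two covariates) that is 42.9/4 ≈ 10.7 events each. The one drawback is that the adjusted odds ratio is conditional and does not correspond to the marginal contrast on which the trial was sized, hence the last item.

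### The secondary aim of comparable motor and functional improvement has no margin, and the test named for the motor score cannot establish it

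*Protocol article*

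**What the plan says.** The aim appears twice in the protocol article. The Abstract wants general anesthesia to "produce comparable symptomatic and functional improvement to surgery under local anesthesia", and the last sentence of the Background section repeats this almost word for word. In both places it stands beside the superiority aim of fewer cognitive, mood and behavioral adverse effects.

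The Statistical analysis section then gives the following:

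- Motor score: "The mean change in MDS-UPDRS Part III scores from baseline to follow-up at 6 months will be analyzed using a two-group" *t* test.
- Further motor analysis: "we will focus on the MDS-UPDRS part III scores at 6 months using multivariable linear regression", with the stratification variable and factors that differ at randomization in the model.
- Other secondary outcomes, which include the functional ones: "we will use the appropriate parametric and nonparametric statistics".
- Threshold: *P* "values < 0.05 will be considered statistically significant".
- Intervals: "In all analyses, statistical uncertainty will be expressed with 95% CIs".
- Per-protocol and as-treated analyses in addition to intention-to-treat, and a full analysis plan to be approved before unblinding.

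The Sample size calculation section covers only the primary composite outcome. The article contains no non-inferiority or equivalence hypothesis, no margin, and no statement of what would count as comparable.

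**The concern.** An aim of comparability asks whether a loss large enough to matter can be ruled out. A two-group *t* test asks whether the difference is zero. A significant result would count against comparability. A non-significant one leaves the question open, because it may reflect a small difference or a wide interval. As the article stands, neither the named test nor the stated threshold can support the aim.

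The aim also has content. The arms differ in how electrode placement is checked. Under local anesthesia the decision uses MRI, microelectrode recordings and the effects of intraoperative stimulation. Under general anesthesia the last of these is absent: "In contrast to the local anesthesia group, no macroelectrode stimulation will be performed". Whether motor benefit is kept without it is a question that readers will expect the trial to answer. If comparable is defined only after the difference and its interval are known, the answer will carry little weight.

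**Working it through.** **1. The plan's own sample size.** Inputs from the Sample size calculation section: 52% versus 26%, two-sided α 0.05, power 0.80, chi-square test.

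n per arm = [1.960·√(2·0.39·0.61) + 0.842·√(0.52·0.48 + 0.26·0.74)]² / 0.26² = (1.352 + 0.560)² / 0.0676 ≈ 54.1, rounded up to 55, so 110 in total. Power at 55 per arm is 0.807. The stated figure reproduces, without continuity correction. It concerns the composite outcome only and says nothing about the motor comparison.

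**2. Precision of the motor comparison.** Input from the article: 55 per arm. The SD of the MDS-UPDRS part III change is not given, so results are in SD units and then in points for assumed SDs of 10, 12 and 15.

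- Standard error = SD·√(2/55) = 0.191 SD.
- 95% CI half-width = t(0.975; 108 df) × 0.191 SD = 1.982 × 0.191 SD = 0.378 SD.
- In points: 3.8, 4.5 and 5.7.

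**3. What the *t* test does when general anesthesia is truly worse.** Power from the noncentral *t* distribution, 108 df, noncentrality = loss / 0.191 SD:

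| True loss (SD) | Power | Chance of a non-significant result |
|---|---|---|
| 0.2 | 18% | 82% |
| 0.3 | 34% | 66% |
| 0.4 | 55% | 45% |
| 0.5 | 74% | 26% |

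The test reaches 80% power at about 0.54 SD, that is 5.4, 6.5 and 8.1 points for the three assumed SDs.

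**4. What 110 patients could support under a non-inferiority reading.** One-sided α 0.025, true difference zero, 55 per arm. Under the normal approximation, power = Φ(margin/0.191 SD − 1.960):

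| Assumed margin (SD) | Power with 110 patients | Total N for 80% power |
|---|---|---|
| 0.2 | 18% | 786 |
| 0.3 | 35% | 350 |
| 0.4 | 55% | 198 |
| 0.5 | 75% | 126 |
| 0.54 | 81% | 108 |
| 0.6 | 88% | 88 |

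The margin at which 110 patients give 80% power is (1.960 + 0.842) × 0.191 SD ≈ 0.53 SD by this approximation, and about 0.54 SD with the *t* distribution. The margins in the table are illustrations. The article offers none, and this check does not choose one.

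All these figures assume complete data in 55 patients per arm. Covariate adjustment may reduce the residual SD and so narrow the interval in points. The results in SD units then apply to that smaller SD.

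**The case against.** **Much of the machinery is already there.** The article promises 95% CIs throughout, an adjusted model for the motor score, per-protocol analyses, and a full analysis plan before unblinding. This stands, and it makes the repair small. It does not remove the point. An interval needs a limit to be read against, and the article itself pairs the aim with a test of zero difference. That is a mismatch within the stated text, not a detail left for later.

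**The article does not say how a non-significant result will be read.** A reader might infer that *P* above 0.05 will be taken as proof of comparability, since the 0.05 threshold is the only rule given. The text does not support that inference: it says what counts as significant and attaches no meaning to the rest. The point here is only that such a result could not support the aim.

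**The *t* test is not named for everything.** A reader might take it to cover functional outcomes too. It is named only for MDS-UPDRS part III. The functional outcomes have no named test, and also no margin.

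**The aim is secondary.** This is correct. The primary superiority hypothesis, its chi-square test and its sample size agree with one another. The article states no rule that makes a change of technique depend on the motor result.

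**A motor loss is not established.** The Background section reports overall comparable motor scores in earlier literature, and the general anesthesia arm keeps MRI and microelectrode guidance. This stands. The figures above give the chance of a non-significant result if a given loss exists. They do not say that a loss is likely, nor that any particular loss is clinically important.

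**Conclusion.** The point holds as a mismatch between a stated secondary aim and the analysis named for it. The aim is comparable symptomatic and functional improvement. The motor analysis tests for a difference, the functional analyses are unspecified, and no margin is given for either. With 55 per arm the 95% CI half-width is about 0.38 SD, and a true loss of 0.4 SD would be non-significant in about 45% of trials, so a non-significant result would not support the claim. The figures in points rest on assumed SDs of 10 to 15; those in SD units need only the planned 55 per arm with complete data.

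This should be fixed, but it does not threaten the primary analysis. The text does not support the stronger conclusions that the trial will declare comparability from a large *P* value, or that a motor loss is to be expected.

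**What to change.** Choose one of two routes and write it into the analysis plan.

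1. **Keep the claim.** Before unblinded outcome data reach anyone who sets the margin, the clinical team fixes and justifies a margin for MDS-UPDRS part III. This matters because the data and safety monitoring board assesses unblinded data at the half-way interim and may advise on design. Conclude comparable only if the 95% CI for the group difference from the already planned adjusted model excludes a loss larger than the margin, in both the intention-to-treat and per-protocol sets. State that 110 patients give 80% power only for a margin of about 0.54 SD or wider, assuming no true difference. Unless functional outcomes are given their own margins, report them descriptively and limit the claim to the motor score.
2. **Drop the claim.** Label the motor and functional comparisons descriptive, report each estimate with its 95% CI, and remove comparable from the aims and conclusions.

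The cost is wording and, for the first route, one clinical decision. Neither needs extra patients or visits as long as the stated power is accepted; a margin narrower than about 0.54 SD would leave power below 80% at the present size. The downside of the first route is that comparability may not be shown.
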